### Inclusion Criteria

Children participating in this study must meet the following criteria: (1) be aged 6 to 17 years; (2) have received the dentist’s recommendation to participate; (3) need to undergo any dental procedure; and (4) be accompanied by a parent or legal guardian who can read, write, and understand either French or English.

### Exclusion Criteria

Participants will be excluded from this study if they (1) are diagnosed with epilepsy; (2) have paralysis or paresis of the hand; (3) have any diagnosed eye disease or problem; or (4) have any other conditions preventing them from using VR (eg, epidermolysis bullosa). Patients with a strong history of motion sickness will not be excluded from this study, but this information will be documented, and additional monitoring will be provided. The use of medication (opioid and nonopioid analgesics, antiemetics, anxiolytics, or any other drugs) prior to the procedure within the last 4 hours will not exclude participants from this study, but this information will be collected before the procedure and included as part of the sociodemographic and clinical information form. Patients who have received previous dental procedures at the recruiting setting will not be excluded.

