### Randomization and Allocation

Randomization will be performed using the electronic REDCap (Research Electronic Data Capture; Vanderbilt University) system. Allocation to either intervention will be randomized by an independent biostatistician from the Unité de recherche clinique appliquée (Applied Clinical Research Unit). To equalize participants across both arms, permuted block randomization with randomly selected block sizes design will be used to randomize participants to their intervention [29]. Access to the randomization list will be granted only to the biostatistician, and allocation will be concealed in REDCap to reduce selection bias.

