### Measures and Outcomes

#### Sociodemographic and Clinical Characteristics

Sociodemographic characteristics will be collected in the waiting room, after consent and prior to the intervention, by the parent or legal guardian present, including age, sex, ethnicity, and the procedure needed. Other clinical information will also include the participant’s clinical diagnosis and any medication taken within the last 4 hours (name, class, and posology) that could affect the study’s outcome. Participants will also be asked if they have taken any medication (name) for attention or hyperactivity to assess its potential impact on their ability to be distracted by VR.

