### Statistical Analysis

The primary analyses for this study will follow an intent-to-treat approach, using randomization status as the independent variable, and the mean difference in anxiety (using the anxiety subscale of the Venham) during the dental procedure (T1) and the SAA mean difference between T0 and T2 as the primary outcomes. As there are two primary outcomes (anxiety subscale and SAA), a Bonferroni correction will be applied, and a significance level of *P*=.025 will be used to determine statistical significance of primary outcomes. An ANCOVA, adjusting for unequal variances and adjusted for the time of the procedure, age, and baseline (T0) anxiety or behavioral score, will be used to assess the mean difference in Venham anxiety score during the dental procedure (T1) between the experimental and the control groups. An ANCOVA, adjusted for time of procedure, neurodevelopmental diagnosis, age, and baseline SAA level (T0), will be used to assess the mean difference in SAA level between groups 10 minutes after the procedure (T2).

For the secondary outcomes analyses, parametric tests adjusted for procedural type, age, sex, and parental presence will be used. Comparisons of dichotomous variables, including the necessity of procedural retakes, the use of other nonpharmacological interventions, and the occurrence of side effects, will be assessed using the Cochran-Mantel-Haenszel test. We will also perform subgroup analyses by age group (6‐12 y vs 13‐17 y) and sex and gender (boys, girls, or other) using ANCOVA. Any side effects will be reported using the Medical Dictionary for Regulatory Activities terminology [42], and their proportions will be compared between groups.

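### Recent medication is recorded as able to affect the outcome but is a covariate in neither primary ANCOVA, which forgoes some precision and leaves chance imbalance unadjusted

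*Protocol article*

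**What the plan says.** All references are to the protocol article.

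- **Exclusion Criteria.** Analgesics, antiemetics and other drugs are listed, and the sentence ends: "anxiolytics, or any other drugs) prior to the procedure within the last 4 hours will not exclude participants from this study". The use is noted: "this information will be collected before the procedure and included as part of the sociodemographic and clinical information form".
- **Sociodemographic and Clinical Characteristics.** The form collects "any medication taken within the last 4 hours (name, class, and posology) that could affect the study’s outcome". Medication for attention or hyperactivity is recorded separately, with the stated aim of judging whether it alters how well VR can distract the child.
- **Statistical Analysis, Venham anxiety score (VARS).** The ANCOVA is "adjusted for the time of the procedure, age, and baseline (T0) anxiety or behavioral score".
- **Statistical Analysis, SAA.** "An ANCOVA, adjusted for time of procedure, neurodevelopmental diagnosis, age, and baseline SAA level (T0") is the full covariate list.
- **Statistical Analysis, secondary outcomes and subgroups.** For secondary outcomes, "parametric tests adjusted for procedural type, age, sex, and parental presence will be used". For subgroups, "We will also perform subgroup analyses by age group", and also by sex and gender.
- **Randomization and Allocation.** "permuted block randomization with randomly selected block sizes design will be used", with no mention of stratifying by medication.

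**The concern.** The article names a variable that it believes can move the outcome, collects it in detail, and then fixes two primary covariate lists that omit it. The lists are written out rather than deferred to another document, so this can be judged from what is shown.

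A prognostic baseline variable left out of an ANCOVA has two costs. The outcome variation it explains stays in the residual, so the treatment estimate is less precise than it could be. And if one arm happens to contain more recently medicated children, nothing in the model corrects for it. Randomization is not stratified on the variable, so such a difference can arise by chance. The sample size is set at about 80% power with little reserve, so a nearly free gain is worth taking.

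**Working it through.** **1. Inputs.** From Sample and Setting: change in log SAA of 0.171 (SD 1.05) in controls and −0.096 (SD 0.495) with VR; 182 per group; two-sided α of .025 after Bonferroni; t test with unequal variances. The documents do not give the share of children medicated within 4 hours, the size of any medication effect, or the VR effect in medicated children. These are assumed below over a range.

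**2. The plan's own figure.** Difference = 0.171 + 0.096 = 0.267. Standard error = √[(1.05² + 0.495²)/182] = √(1.3475/182) = 0.0860. Noncentrality = 0.267/0.0860 = 3.10. With Satterthwaite df of about 258 and α = .025, power is 80.1%, and 182 per group is the smallest size reaching 80%. The stated 364 is reproduced.

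**3. Precision forgone.** Let a share p be medicated and let medication shift the outcome by k SD in each arm. The variable then explains R² = p(1 − p)k² of the variance. Adjusting for it multiplies both SDs by √(1 − R²).

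| p | k | R² | Power with adjustment |
|---|---|---|---|
| 5% | 0.25 | 0.0030 | 80.3% |
| 10% | 0.5 | 0.0225 | 81.1% |
| 20% | 0.8 | 0.1024 | 84.6% |

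The starting point is the t test that sized the trial. The planned covariates, T0 SAA above all, may already carry part of this information, and the gain shrinks to that extent.

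**4. Chance imbalance.** The SD of the between-arm difference in medicated share is √[2p(1 − p)/182], or 2.3, 3.1 and 4.2 percentage points for p = 5%, 10% and 20%. Multiply by k and by the root-mean-square SD, √(1.3475/2) = 0.821. For the three rows above, a one-SD imbalance moves the unadjusted estimate by 0.0047, 0.0129 and 0.0275 log units, about 2%, 5% and 10% of 0.267. It can go in either direction.

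**5. A separate quantity: a smaller VR effect in medicated children.** If they receive a fraction r of the benefit, the average difference is 0.267 × [1 − p(1 − r)].

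| p | r = 0 | r = 0.5 | r = 1 |
|---|---|---|---|
| 5% | 75.6% | 77.9% | 80.1% |
| 10% | 70.5% | 75.6% | 80.1% |
| 20% | 59.1% | 70.5% | 80.1% |

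Entries are power at 182 per group with SDs unchanged. Nothing in the documents selects a row or a column. A main-effect covariate does not change the average difference in this table.

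**The case against.** The case for leaving the plan alone has real force.

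- **No bias.** Both primary analyses are randomized intent-to-treat comparisons, and omitting a baseline covariate does not bias them. This stands in full, and it limits the point to precision and chance imbalance.
- **Baseline values already adjust.** A drug taken beforehand may already act at T0, and both models include the T0 value. This stands in part. For SAA, T0 may take up a shift in level but not necessarily a blunted response. For VARS it helps little: the pilot T0 mean was 0.08 (SD 0.28) against 0.625 (SD 1.35) during the procedure, so a T0 score that is nearly always zero says little about a drug acting later.
- **The data are not idle.** The Abstract plans descriptive and comparative statistics for clinical data, so medication would be tabulated and an imbalance seen. That is correct, but seeing an imbalance does not adjust for it, and adding the covariate only then would be post hoc.
- **Broad eligibility is deliberate.** VR is presented as an additional tool, and drug treatment is allowed as indicated in both arms. This stands, and the point asks for no change to who is enrolled.
- **A fuller plan may cover it.** Supportive analyses by medication are commonly left to a statistical analysis plan, and their absence here is not a fault. The primary covariates are different because the article itself lists them.

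**Conclusion.** The article says recent medication could affect the outcome, yet neither primary ANCOVA adjusts for it. The loss is modest. Under the assumed 5% to 20% medicated and 0.25 to 0.8 SD shift, SAA power would rise from 80.1% to between about 80.3% and 84.6%, and a typical chance imbalance would move the estimate by roughly 2% to 10% of the planned difference. No corresponding figure is calculated for VARS. This is a low-cost improvement, not an error that invalidates the analysis.

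A reader might go further and infer that admitting medicated children, with medication left out of the models, dilutes both primary comparisons. The documents do not support that. Dilution would need VR to work less well in medicated children and a material share of them, and neither figure is given. The opposite direction is also possible, since medicated children may be the more anxious ones with more to gain. The power figures of 59% to 76% describe only the extreme case of no VR benefit in them; at half the benefit the range is 71% to 78%, and at the full benefit power stays at 80%. Nor would the covariate be the cure, because dilution comes from effect modification and a main-effect term leaves it in place.

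**What to change.** Keep eligibility as it is. Before the data are analysed, add recent anxiolytic or opioid use (yes/no within the 4-hour window) as a baseline covariate in both primary ANCOVAs. Define it from what was taken and recorded before allocation. The article says the information is collected before the procedure, so the timing relative to allocation should be confirmed.

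A medication-by-arm interaction, or an analysis restricted to children without these drugs, may be prespecified as supportive only. Making the trial's claim rest on the unmedicated subset would change the target population, so the conclusion should stay with the full intent-to-treat comparison.

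The cost is one degree of freedom in each model, with no new data collection. Timing matters: staff are not blinded, 300 children had been recruited by November 2025 and results are expected in June 2026, so the choice is credible only if it is documented before outcomes are examined by arm.

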### Randomization and Allocation

Randomization will be performed using the electronic REDCap (Research Electronic Data Capture; Vanderbilt University) system. Allocation to either intervention will be randomized by an independent biostatistician from the Unité de recherche clinique appliquée (Applied Clinical Research Unit). To equalize participants across both arms, permuted block randomization with randomly selected block sizes design will be used to randomize participants to their intervention [29]. Access to the randomization list will be granted only to the biostatistician, and allocation will be concealed in REDCap to reduce selection bias.

### Interventions

#### Control Intervention

Participants assigned to the control intervention will only receive the care-as-usual approach. This includes viewing cartoons on a muted, mounted television already set by the clinic, watching a video of their choice on a tablet on YouTube, and the use of pharmaceutical treatment during the procedure, such as injected local anesthesia, if indicated by the procedure. In the event of noncooperation during the appointment, any necessary procedural retakes or rescheduling of appointments as determined by the dentist will be documented by the research assistant. One parent will be permitted to be present in the room during the procedure as part of the clinic’s usual protocol, and their presence will be recorded. Children in the control intervention will be offered the option to try the VR game after the study period, if they choose to do so.

#### Experimental Intervention

Participants assigned to the experimental intervention will engage with a VR game called “Dream Dental,” tailored for a pediatric population. The simplified no-success game, developed by Paperplane Therapeutics [30], is enjoyable regardless of a child’s video game experience, and its point-and-shoot arcade style makes it easy to understand (Figure 1). It was designed specifically for this study, with the horizontal position required for dental procedures in mind (Figure 1). The VR video game aims to reduce anxiety in children aged 6 to 17 years by means of immersive distraction.

**Figure 1. F1:**
[figure not shown]
Patient’s position during a dental procedure and virtual reality accessory [30]. The images or screen captures were reproduced with permission from Paperplane Therapeutics.

We will use a lightweight head-mounted device (HMD; Pico Neo 4) with built-in eye tracking [31]. The Pico Neo 4 is a standalone VR headset featuring a 4K Super-Vision Display with pancake lenses for a clearer, broader field of view. Its key features include a balanced design with a rear-mounted battery, a high-resolution display (2160×2160 per eye), a 90 Hz refresh rate, and full-color pass-through via its 16 MP RGB camera. It also uses 6 degrees of freedom inside-out tracking and offers both wireless and wired PC VR connectivity. This headset was specifically designed to be lightweight and smaller to better fit children’s smaller heads. Children can play throughout the entire dental procedure using a clicker in one hand (Figure 1); eye-tracking sensors will assist navigation through the game, but will not be used for data collection. The VR game “Dream Dental” features a rail mechanism (predefined path or sequence of scenes to reduce body and head movement) that guides children through an interactive environment filled with entertaining characters. The game is designed for dental procedures (Figure 2) and incorporates innovative eye-tracking technology integrated into the headset. This technology simplifies navigation by enabling users to target objects with their eyes instead of relying on head movements. The goal is to make the game easier to use during dental procedures, where head movements need to be restricted. These features are also intended to reduce virtual motion sickness. The VR HMD allows children to view the game they are playing in real time while blocking their view of the procedure, and it was determined not to hinder dental procedures [27].

**Figure 2. F2:**
[figure not shown]
Dream Dental game environment [30].

Pharmaceutical treatment during the procedure, such as injected local anesthesia, will be used as indicated. In the event of noncooperation during the appointment, any procedural retake or rescheduled appointments will be noted by the research assistant or resident dentist. One parent will be allowed in the room during the dental procedure, and their presence will be recorded.

#### Study Time Periods

The study time periods are as follows and are detailed in Table 3. T0 corresponds to the time before the start of the intervention, T1 represents the time during or at the midpoint during the procedure, and T2 corresponds to the period 10 minutes after the intervention.

**Table 3. T3:** Study time periods and outcomes.

Study time periods	Outcomes									
	Patients’ SDC^a^	VARS^b^ anxiety	SAA^c^	Parents’ and health care professionals’ satisfaction	Patients’ satisfaction	Patients’ physiological parameters	VBRS^d^ behavior	Side effects	Length of procedure	FLACC-R^e^
T0^f^	✓	✓	✓			✓	✓	✓		✓
T1^g^		✓				✓	✓			✓
T2^h^			✓	✓	✓	✓		✓	✓	

a SDC: sociodemographic characteristics.

b VARS: Venham Anxiety Rating Scale.

c SAA: salivary alpha-amylase.

d VBRS: Venham Behavioral Rating Scale.

e FLACC-R: Face, Legs, Activity, Cry, and Consolability—Revised.

f T0: before the procedure.

g T1: midpoint during the procedure.

h T2: 10 minutes after the procedure.

### Measures and Outcomes

#### Sociodemographic and Clinical Characteristics

Sociodemographic characteristics will be collected in the waiting room, after consent and prior to the intervention, by the parent or legal guardian present, including age, sex, ethnicity, and the procedure needed. Other clinical information will also include the participant’s clinical diagnosis and any medication taken within the last 4 hours (name, class, and posology) that could affect the study’s outcome. Participants will also be asked if they have taken any medication (name) for attention or hyperactivity to assess its potential impact on their ability to be distracted by VR.

#### Primary Outcomes

The two primary outcomes of this study are to measure both observed and objective biomarker-based indicators associated with DFA.

#### Measures of Primary Outcomes

The first primary outcome will evaluate DFA using the VARS (Table 1) [25]. The VARS is an observation-based assessment by proxy for DFA and is among the most frequent anxiety scoring instruments for DFA [25]. The scale has been used as an anxiety rating scale in other studies that evaluated the efficacy of VR distraction in the management of DFA [32,33]. The anxiety scale consists of one item, with six defined anxiety levels that range from 0, representing the child being relaxed, smiling, and willing to cooperate, to 5, representing the child being out of contact with the reality of the threat. The highest score represents the highest anxiety level [25]. A high degree of reliability was observed for this scale, even by untrained observers [25,34]. A research assistant will indicate a score from 0 to 5 on the anxiety scale at T0 and T1 (Table 3).

The second primary outcome will assess the mean difference in SAA levels between T0 and T2, 10 minutes after the dental procedure. This enzyme is linked to both adrenaline and noradrenaline and is a validated and reliable specific biomarker of autonomic nervous system activity. It has been proposed as an alternative biomarker for anxiety, over salivary cortisol, as it reaches peak levels within 10 minutes after a stressful procedure compared to cortisol, which requires a 30-minute delay [16,35]. Enzyme sampling has been performed in previous studies to evaluate DFA in children undergoing dental procedures [35-37]. This enzyme is considered an accurate and noninvasive procedure for assessing anxiety-related events such as dental examination, cleaning, restoration, or extraction in children [26,35]. Alpha-amylase sampling has been performed in previous studies to evaluate DFA for children undergoing dental procedures [35,38]. Salivary samples will be collected using a sterile dental cotton swab from under the tongue and stored immediately within a sterile vial in a research-specific on-site freezer at −80 degrees Celsius. The research assistant will collect the samples and take them to the laboratory. Results will be entered in REDCap for analysis purposes after the study.

#### Secondary Outcomes

The secondary outcomes include (1) parents’ and health care professionals’ satisfaction in both groups and children’s satisfaction in the VR intervention; (2) changes in physiological parameters, such as heart rate and oxygen saturation during and after the intervention compared to baseline; (3) behavior during the procedure; (4) occurrence of side effects (nausea, dizziness, and vomiting); (5) length of the procedure; and (6) the effectiveness of VR in reducing pain (Table 3).

#### Measures of Secondary Outcomes

The secondary outcomes will be measured as follows:

Parents’ or legal guardians’ satisfaction with the intervention will be assessed using a Numerical Rating Scale (0‐10, where 0 is very dissatisfied and 10 is very satisfied) and according to the recommended question by the Pediatric Initiatives on Methods, Measurement and Pain Assessment in Clinical Trials: “Considering anxiety relief, side effects, and emotional recovery, how satisfied were you with the intervention used to manage anxiety experienced by your child?” [39] (Multimedia Appendix 1).Health care professionals’ satisfaction with the intervention will be assessed using a 6-question satisfaction questionnaire, with a range of scores from 1 to 4 (1=“Totally disagree,” 2=“Disagree,” 3=“Agree,” and 4=“Totally agree”; Multimedia Appendix 2).Child satisfaction with VR will be assessed using a 0‐10 numerical rating scale (where 0 is very dissatisfied and 10 is very satisfied; Multimedia Appendix 1).Physiological parameters (heart rate and oxygen saturation) will be measured using the COVIDIEN Nellcor pulse oxygen saturation meter, an approved and validated device.The patient’s behavior during the procedure will be assessed by proxy via a research assistant using the Venham Behavioral Rating Scale at T0 and T1 (Table 3) [25,40]. This 6-point scale assesses children’s behavior and provides information about patients with disruptive behavior. The scale points are based on objective, and readily observable behaviors and classify children’s behavior into 6 categories ranging from 0 (total cooperation) to 5 (general protest, no compliance, or cooperation). This scale has demonstrated good interrater reliability and has proven to be a valuable instrument for assessing children’s behavioral responses to dental procedures [40].Side effects will be collected in children in both groups from arrival on site until discharge, using a checklist of side effects commonly associated with VR, namely nausea, dizziness, and vomiting. Any of these side effects will be recorded along with the time they will occur.The length of the procedure in minutes will be measured and recorded for each participant and compared between the two groups.Pain will be assessed using the Face, Legs, Activity, Cry, and Consolability—Revised scale (FLACC-R) [41] (Multimedia Appendix 3). This questionnaire will serve to assess VR efficacy in reducing pain by comparing the mean pain level of both groups (experimental and control intervention) during the dental procedure (T1).

The FLACC-R scale (Multimedia Appendix 3) is a tool developed by Malviya et al [41] to assess pain in infants and young children who are unable to communicate their pain verbally. Health care professionals use this scale to evaluate pain in children who may not be able to express their discomfort in words. The FLACC-R scale consists of five categories, each rated on a scale of 0 to 2, with 0 indicating no pain and 2 indicating severe pain. The categories are as follows:

*Face* (F): this category assesses the child’s facial expressions. It looks at whether the child is relaxed, smiling, or showing pain-related facial expressions, such as frowning, grimacing, or jaw clenching. A score of 0 indicates a relaxed face, while a score of 2 indicates a highly distressed or painful expression.*Legs* (L): this category considers whether the child’s legs are relaxed or whether there is increased movement, kicking, or tensing of the leg muscles. A score of 0 implies relaxed legs, while a score of 2 indicates significant leg movement due to pain.*Activity* (A): this category looks at whether the child is calm and content or if they are restless, agitated, or unable to stay still. A score of 0 indicates calmness, while a score of 2 indicates high activity and restlessness due to pain*.**Cry* (C): this category assesses the quality of the child’s cry, considering whether the child is not crying, whimpering, or having a high-pitched, continuous cry. A score of 0 means no crying, while a score of 2 implies a high-pitched, continuous cry*.**Consolability* (C): the *consolability* considers whether the child can be comforted easily or if they remain inconsolable despite efforts to soothe them. A score of 0 suggests easy consolability, while a score of 2 indicates that the child cannot be consoled.

The total score on the FLACC scale is obtained by summing the scores across the 5 categories and ranges from 0 (no pain) to 10 (severe pain). The FLACC-R score will be evaluated at T0 (baseline) and at 10 minutes after the start of the procedure or at midprocedure for shorter dental treatments (T1).

